**Demographic information and pre-treatment characteristic analysis method**
Descriptive statistics will be conducted for demographic information and characteristics. Continuous data will be expressed using the number of observations, mean, standard deviation, median, 25% quantile, and 75% quantile. Categorical data will be expressed using frequency and percentage. For continuous data, independent *t*-test will be conducted to test the mean difference between groups if normality assumption is satisfied. If normality assumption is not satisfied, Wilcoxon's rank sum test will be conducted. Chi-Squared test will be conducted to test the mean difference between groups. If more than 25% cells have an expected frequency of less than 5, Fisher's exact test will be conducted.
2.

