**Efficacy evaluation**
In the efficacy evaluation, ITT will be treated as the main analysis group, and PP sets will be treated as the secondary analysis group. All statistical analysis will be conducted as two-sided tests with a significance level of 5%. Two-sided 95% confidence interval will be presented. Descriptive statistics will be presented for each treatment group and visit. Descriptive statistics and 95% confidence intervals will be presented for differences between the baseline and each visit.

Among efficacy evaluation variables, missing values of continuous variables will be analyzed using baseline observation carried forward correction.

A. Analysis of primary endpoints

For symptoms of lumbosacral radiculopathy at each measurement time point, descriptive statistics (number of patients, mean, and standard deviation) of the ODI score and changes in ODI at the end of treatment (4 weeks) and follow-up (8 weeks) compared with the baseline will be presented.

Paired *t*-test or Wilcoxon's signed ranked test will be conducted for intra-group changes in ODI at the end of treatment (week 4) compared with the baseline (0) depending on the satisfaction of normality. An analysis of variance model that includes changes in ODI at the end of treatment compared with the baseline as effects and baseline ODI as covariates will be used to evaluate the effects in the treatment group compared with the control group. Differences in least-square mean between treatment and control groups will be calculated, and two-sided 95% confidence interval and *P* value for the differences will be presented.

B. Analysis of secondary endpoint

Changes in ODI at follow-up (8 weeks) compared with baselineAssessment of subjective pain intensity in patients with lumbosacral radiculopathy-Lumbosacral radiculopathy pain will be divided into lower back and lower extremity pain using NRS, MPQ, and K-RMDQAssessment of quality of life related to lumbosacral radiculopathy-Evaluation of overall quality of life using EQ-5D. The same analysis methods for primary endpoints will be used to analyze secondary endpoints

C. Exploratory efficacy evaluation

Evaluation related to additional NBT or surgery after completion of the study

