**Rate of early termination = (patients who completed the study early/patients who completed the entire study)∗100**

Analysis of rescue medication use

Independent t-test or Wilcoxon's signed rank test will be conducted to compare the number and dose of use according to different types of rescue medication between the groups.

D. Classification and post hoc analysis of responders and nonresponders

Definition of responders

(1)Those with a minimal CID decrease of NRS 2.5 from the baseline to the date of evaluation. Therefore, responders will be defined as follows. For example, pain reduction of greater than NRS 2.5 will be defined as CID, and CID will be used to divide patients into responders and nonresponders.(2)Using the previously described criteria, patients who had improved symptoms and completed the study early will be considered as responders.

Post hoc analysis

Adequate post-hoc analysis will be conducted by a statistician for differences in treatment results for each treatment group using the responder and non-responder criteria.

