**3. Safety assessment**

Descriptive statistics will be conducted to analyze PRO-CTCAE questionnaire items, number of adverse events, number of patients with adverse events, severity of events, and causal relationship of adverse events with the intervention for each dose group. Nonparametric methods may be used if necessary.

Vital signs, physical examination results, and subjective complains of patients will be comprehensively reviewed to perform statistical analysis on items that are considered clinically significant by the researcher. Continuous variables will be presented using the number of observations, mean, standard deviation, median, and minimum/maximum values, and differences in the mean between the 2 groups will be analyzed using paired *t*-test or Wilcoxon's signed rank test. Chi-Squared test or Fisher Exact test will be conducted for analysis of adverse events. Moreover, clinically significant changes will be compared between groups through generalized estimating equation analysis to assess statistical significance.

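### Paired tests are named for between-group comparisons of continuous safety variables, and for the nonparametric comparison of rescue medication, in a trial of two independent arms

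*Protocol article*

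**What the plan says.** All references are to the protocol article.

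- **Section 2.9, Safety assessment.** For continuous variables, "differences in the mean between the 2 groups will be analyzed using paired" t-test or Wilcoxon's signed rank test. The same section uses the chi-squared or Fisher exact test for adverse events, and adds that "clinically significant changes will be compared between groups through generalized estimating equation analysis to assess statistical significance".
- **Section 2.9, Analysis of rescue medication use.** "Independent t-test or Wilcoxon's signed rank test will be conducted to compare the number and dose of use" by type of rescue medication between the groups.
- **Section 2.9, Demographic information and pre-treatment characteristics.** Two-group comparisons of continuous data use the independent t-test or, without normality, "rank sum test will be conducted" in Wilcoxon's form.
- **Section 2.9, Efficacy evaluation, A.** The paired t-test or signed rank test is used for change within a group. The between-group comparison is by ANOVA, described as a "model that includes changes in ODI at the end of treatment compared with the baseline as effects and baseline ODI as covariates". It then says: "Differences in least-square mean between treatment and control groups will be calculated", with a 95% confidence interval and P value.
- **Sections 2.2 and 2.6.** The design is two-arm and parallel, with 1:1 block randomization. No matching is described.

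**The concern.** The paired t-test and the signed rank test both work on one difference per pair. Here each arm contains different people and nothing links a patient in one arm to a patient in the other. For continuous safety variables both named options are paired tests, so neither branch fits the comparison. For rescue medication only the nonparametric branch is wrong.

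Safety is part of the hypothesis in section 1.1, so its between-group test should be usable as written. An analyst who follows the text must either depart from the protocol or invent a pairing after the data are in. The second course leaves a p-value that another analyst could not reproduce.

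The primary-model sentence has a lesser fault of the same kind. It lists the ODI change among the effects, although it is the response, and does not name treatment group as a term. The secondary endpoints inherit the sentence because they use the same methods.

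**Working it through.** **1. The plan's own figure.** Section 2.3 takes 20 per group and a 20% dropout: 20 / (1 − 0.20) = 25 per group, 50 in total. This reproduces. No effect size, SD or power is stated, so there is no power figure to check.

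**2. The test named in each place.**

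| Comparison (section 2.9) | Parametric option | Nonparametric option | Fits two independent arms? |
|---|---|---|---|
| Baseline, between groups | Independent t | Rank sum | Both fit |
| ODI, within group | Paired t | Signed rank | Both fit the within-group question |
| Rescue medication, between groups | Independent t | Signed rank | Parametric option only |
| Continuous safety, between groups | Paired t | Signed rank | Neither |

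The article makes the distinction correctly in the first two rows and loses it in the last two.

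**3. Unequal arms.** A paired test needs equal numbers. Assume that each of 25 patients per arm is retained independently with probability 0.80, which is the planned dropout applied to both arms. Then P(equal arms) = Σₖ [Bin(k; 25, 0.80)]² = 0.141. As a check, the normal approximation is 1 / (2√π · σ) with σ = √(25 × 0.8 × 0.2) = 2, which gives 0.141.

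The safety set is defined by at least one procedure after randomization, so it may lose fewer patients. With an assumed loss of 10% the same sum gives 0.19, and with 5% it gives 0.27. Unequal arms remain the likelier outcome across this range. Run on arms of 21 and 19, both paired tests stop with an error.

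**4. Equal arms.** With n per arm, the two t statistics share the numerator, the difference in means. They differ in its variance:

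- independent: (s_A² + s_B²) / n
- paired: (s_A² + s_B² − 2·s_AB) / n

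The covariance s_AB is set by which row of one arm sits beside which row of the other. With no true pairs it is an accident of sorting. In one simulated normal data set (20 per arm, 5,000 random re-pairings):

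| Test | p-value | Share of pairings with p < 0.05 |
|---|---|---|
| Independent t | 0.038 | does not depend on pairing |
| Rank sum | 0.036 | does not depend on pairing |
| Paired t, central 95% of pairings | 0.009 to 0.089 | 58% |
| Signed rank, central 95% of pairings | 0.009 to 0.133 | 52% |

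This data set was drawn to sit near the 5% boundary, where row order matters most.

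**5. Error rates under arbitrary pairing.** These come from 4,000 simulated trials per setting, with normal data and a two-sided 5% level. The standardized difference of 0.8 is an assumption, since the article gives none.

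| n per arm | True difference | Independent t | Paired t | Rank sum | Signed rank |
|---|---|---|---|---|---|
| 20 | 0 | 0.043 | 0.045 | 0.041 | 0.043 |
| 25 | 0 | 0.050 | 0.051 | 0.045 | 0.051 |
| 20 | 0.8 | 0.68 | 0.67 | 0.67 | 0.64 |
| 25 | 0.8 | 0.80 | 0.78 | 0.77 | 0.76 |

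Degrees of freedom halve (2 × 20 − 2 = 38 against 20 − 1 = 19; 48 against 24 at 25 per arm). The critical value moves only from 2.02 to 2.09, or from 2.01 to 2.06, which is why so little power is lost.

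**6. The primary model.** The sentence states that its purpose is to compare the treatment group with control, and the next sentence reports a least-squares mean difference between the groups. Such a difference, adjusted for baseline ODI, exists only if group is a factor and ODI change is the response. Read together, the two sentences fix one model: an ANCOVA of week-4 ODI change on group and baseline ODI.

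**The case against.** The strongest reply is that these are slips in naming. The authors use both kinds of test correctly elsewhere in section 2.9. With unequal arms the software would refuse to run, so the error would come to light. The reach is also narrow: in the safety section it covers continuous variables only, among items the researcher considers clinically significant, and rescue medication is an exploratory outcome in a study described as preliminary. All of this is fair and limits the weight of the point. It does not remove it. The safety sentence names the two groups as what is compared, so it cannot be read as within-group change, and an error that surfaces at analysis forces an unplanned choice once the data are visible.

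Four stronger readings are tempting, and the documents do not support them:

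- **That all safety and rescue p-values are affected.** Adverse events have chi-squared or Fisher tests, clinically significant changes have generalized estimating equations, and rescue medication keeps a correct independent t-test.
- **That the primary analysis is invalid or cannot give its treatment contrast.** That takes one clause alone. The stated purpose and the least-squares mean sentence already imply the right model.
- **That halved degrees of freedom cost much power, or that false positives rise.** The simulation shows neither.
- **That the signed rank branch will certainly be used for rescue medication.** Skewed counts with many zeros are plausible, but the article gives no data on this.

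**Conclusion.** The point holds for two stated rules: both tests named for between-group differences in continuous safety variables, and the nonparametric option for rescue medication. The harm is a test that is undefined or not reproducible, rather than a biased one. It cannot be run when the arms differ in size (about 86% of the time under independent 20% dropout from 25 per arm), and it depends on row order when they do not. The percentage rests on the planned dropout applying independently to both arms and falls to roughly 73% at an assumed 5% loss. The row-order figures come from a single simulated data set and show the mechanism, not a typical effect. The primary-model sentence is a drafting error that leaves the primary analysis intact. The corrections should be made before analysis, and the primary result does not hang on them.

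**What to change.** Three changes of wording in section 2.9:

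1. **Safety assessment:** compare continuous variables between groups with the independent t-test or, without normality, the Wilcoxon rank sum test. Keep paired tests for within-group change only.
2. **Analysis of rescue medication use:** replace signed rank with rank sum and keep the independent t-test. This matches the rule already used for baseline characteristics.
3. **Analysis of primary endpoints (clarification only):** name the week-4 change in ODI as the dependent variable, treatment group as the factor and baseline ODI as the covariate.

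The sample size stays at 50, and visits, data collection and trial conduct do not change. The only cost is recording the corrections under the amendment procedure in section 2.9.3.

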### Objective

1.1

The study aims to verify the hypothesis that the concurrent use of a deeply inserted acupotomy needle and NBT is more effective, safe, and cost-effective for lumbosacral radiculopathy than NBT alone.

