### Sample size calculation

2.3

This is a practical clinical study to assess the effects NBT and deeply inserted acupotomy combination treatment on lumbosacral radiculopathy.

In a previous pilot RCT that compared the therapeutic effects of deeply inserted acupotomy and general acupuncture in lumbar disc herniation patients,^[14]^ considering a 20% drop-out rate, a total of 50 patients (25 each in the acupuncture and deeply inserted acupotomy groups) were included.

In another RCT that compared the effects of deeply inserted acupotomy and general acupuncture in lumbar disc herniation patients,^[15]^ a total of 40 patients (20 each in the acupuncture and deeply inserted acupotomy groups) were included.

The phase 1 preliminary clinical study that will be conducted aims to estimate the mutual effects of NBT and deeply inserted acupotomy combination treatment and assess whether the combination treatment is effective and safe compared with conventional treatment. Thus, the study must be conducted with a minimum number of patients within the limit that satisfies the study purpose. Currently, there is no previous study that has provided the same intervention. Therefore, based on previous studies that provided similar treatment interventions and involved disease groups as in our study, 20 patients were included in each group. Considering a dropout rate of 20%, a total of 50 patients (25 patients in each group) was set as the target sample size.

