### Recruitment, randomization, blinding, and nonblinding

2.6

Advertisements for patient recruitment will be posted on the Catholic Kwandong University, International St. Mary's Hospital's bulletin boards, along with posters, banner advertisements, and internet cafes. All advertisements will be run after institutional review board (IRB) approval.

Individuals who provide written consent to participate in the study will be assigned a screening number, according to the order of the outpatient visit at screening. Unblinded sub-investigators, who do not influence the research results and analysis, will refer to the randomization list that has been prepared by a commissioned professional statistician, and assign participation numbers. Participants will be allocated to the NBT group and the acupotomy + NBT group in a ratio of 1: 1. A block randomization table will be generated by an independent statistician and patients will be assigned to one of 2 groups according to the randomization table. Screening numbers, randomization numbers, and initials assigned to each participant will be used as subject identification codes to identify the participant until the end of the clinical trial.

The NBT used in this study is not a clinical investigational product and does not require allocation concealment, since it is administered to all groups. Moreover, it is impossible to blind the investigator and the participant in each group due to the nature of the study intervention, which is based on the contact between the patient and the medical staff. Instead, the investigator maintains blinding to prevent bias in evaluating the participant. After the clinical trial is completed, all clinical report forms (CRFs) will be collected, the database process terminated, and unblinding performed, if required for statistical analysis. Moreover, if it is deemed necessary to confirm the subject group due to an emergency situation during the clinical trial, the randomization code will be disclosed only to the participant, according to the principal investigator's discretion. If it is not possible to consult with the principal investigator and the situation is urgent, the randomization code of the subject will be disclosed after consultation with the randomization code officer. If unblinding is performed, the documentation of the reason for the unblinding will be retained, and the participant with the disclosed randomization code will not be able to continue the trial.

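### The plan sets out to verify that acupotomy + NBT is safe compared with NBT alone, but its between-arm safety analyses are tests of no difference, with no margin and no stated interval for the adverse-event difference, in at most 25 patients per arm

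*Protocol article*

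**What the plan says.** Section 1.1 (Objective) sets out to verify a hypothesis: that the combination "is more effective, safe, and cost-effective for lumbosacral radiculopathy than NBT alone". Section 2.3 (Sample size calculation) says the trial will "assess whether the combination treatment is effective and safe compared with conventional treatment". The same section calls it a preliminary study: "The phase 1 preliminary clinical study that will be conducted aims to estimate the mutual effects of NBT and deeply inserted acupotomy combination treatment".

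On size, Section 2.3 takes its number from earlier studies of similar treatments: "20 patients were included in each group". It then adds: "Considering a dropout rate of 20%, a total of 50 patients (25 patients in each group) was set as the target sample size". Allocation is 1:1 (Section 2.6).

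The Safety assessment in Section 2.9 begins with descriptive statistics per group: questionnaire items, numbers of events and of patients with events, severity and causality. Its between-arm analyses are three:

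- for adverse events, "Chi-Squared test or Fisher Exact test will be conducted for analysis of adverse events";
- for continuous safety items, a test of the mean difference between the two groups;
- in addition, "clinically significant changes will be compared between groups through generalized estimating equation analysis to assess statistical significance".

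The two-sided 5% level and the presentation of 95% confidence intervals are both written under Efficacy evaluation.

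**The concern.** A test of no difference can show that harm differs between arms. It cannot show that an excess of harm is absent or tolerably small. For that a plan needs a margin, or at least an interval for the excess whose upper limit is discussed. The Safety assessment states neither, so the document contains no criterion by which its own safety hypothesis could be met.

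The practical risk is a non-significant adverse-event comparison in a small trial being taken as support for safety when the data still allow a sizeable excess. The Discussion expects evidence on safety to help put the combination forward as an alternative used alongside standard NBT, so the safety statement is meant to carry weight.

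**Working it through.** **1. The plan's own figure.** 20 evaluable per arm with 20% dropout: 20 / (1 − 0.20) = 25 per arm, 50 in total. This reproduces Section 2.3. The 20 has no event rate, effect size or power behind it, so there is no power figure for safety to reproduce.

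**2. Inputs.**
- n per arm: 25 is the ceiling. The safety set is ITT patients with at least one procedure, so later dropouts stay in. The evaluable number, 20, is a pessimistic lower value.
- Level: two-sided 5%, from the Efficacy evaluation, where the sentence is worded to cover all analyses.
- Test: Fisher or uncorrected chi-squared. The only rule for choosing between them is stated for baseline data.
- Adverse-event rates: assumptions, as the documents give none.

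**3. Power by exact enumeration.** For true rates p₁ and p₂, power is the sum of Bin(a; n, p₁) × Bin(b; n, p₂) over all tables (a, b) with p < 0.05. The chance of missing the harm is 1 − power.

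| Control v combination | Fisher power, n = 20 / 25 | Chi-squared power, n = 20 / 25 | Missed (range) |
|---|---|---|---|
| 5% v 15% | 0.070 / 0.072 | 0.154 / 0.213 | 79-93% |
| 10% v 30% | 0.242 / 0.305 | 0.357 / 0.450 | 55-76% |
| 20% v 40% | 0.192 / 0.231 | 0.291 / 0.351 | 65-81% |
| 20% v 60% | 0.650 / 0.788 | 0.753 / 0.867 | 13-35% |

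**4. Where a tripling becomes detectable.** Power for p v 3p reaches 50% at these control rates: Fisher 16.3% (n = 20) and 14.4% (n = 25); chi-squared 13.4% and 11.1%. Below about 11% a tripling is missed more often than found whichever test and size apply. Above about 16% it is found more often than missed.

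**5. What a non-significant result leaves open.** Take 2/25 patients with adverse events on NBT and 6/25 on the combination, an observed tripling.
- Fisher p = 0.25.
- Uncorrected chi-squared = 50 × (2×19 − 6×23)² / (25 × 25 × 8 × 42) = 500,000 / 210,000 = 2.38, p = 0.12.
- Risk difference = 0.24 − 0.08 = 0.16. The Wilson limits are 0.115 to 0.434 for 6/25 and 0.022 to 0.250 for 2/25.
- Newcombe lower limit: 0.16 − √[(0.24 − 0.115)² + (0.250 − 0.08)²] = −0.05.
- Newcombe upper limit: 0.16 + √[(0.434 − 0.24)² + (0.08 − 0.022)²] = +0.36.

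Neither test is significant, yet the data are compatible with anything from 5 points fewer to 36 points more patients with adverse events.

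**6. Equal observed rates.** 3/25 v 3/25 gives a Newcombe interval of −20 to +20 points. Identical counts would still not exclude an excess of nearly 20 points.

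**The case against.** **Nothing says that p > 0.05 will be read as safe.** This is true. A reader might infer such a rule, but the document does not state it, and the descriptive adverse-event tables are also planned. The point is narrower: no criterion for safety is stated, and the tests named cannot supply one.

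**The test is not weak at every rate.** Also true. A reader might infer that a tripled rate is always more likely missed than found. That fails above control rates of about 11-16%. Such rates are possible here, because reactions are sought at every visit and worsening of existing symptoms counts (Section 2.8.5). A high background rate does not rescue the test in general, however: 20% v 40% is still missed in 65-81%.

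**A starker example depends on the test.** 2/25 v 8/25 gives Fisher p = 0.07, but the expected counts are 5, 5, 20 and 20, and uncorrected chi-squared gives p = 0.034. It does not illustrate a missed harm and should not be used.

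**Intervals may already be planned.** The 5% level and the 95% intervals stand together under Efficacy evaluation, so one cannot be carried over to safety and the other refused. If both carry over, some safety intervals may be intended. Even so, none is stated for the adverse-event difference, and no use of its upper limit is described.

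**Acupotomy might reduce some events.** Section 2.8.5 expects aggravation of pain to be the main side effect, and the combination could lower it. The Objective can even be read as claiming greater safety, for which a difference test has the right form. With equal arms and two-sided tests the miss rates above then apply in reverse (30% v 10% is missed in 55-76%). A reduction in pain events would also not settle events caused by the added procedure.

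**The trial is preliminary, and an article leaves details to the full plan.** Small size is not the fault, and the exact interval method may be left elsewhere. But the verification wording and the choice of significance tests are both stated here, and they do not match. A preliminary trial is a reason to estimate safety, not to verify it.

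**Conclusion.** The concern holds in this form: the stated aim is comparative safety, the between-arm tools are tests of no difference without a margin or a stated interval for the adverse-event difference, and at most 25 patients per arm cannot verify safety by that route. The mismatch itself does not depend on any assumed rate. Its size does. Under the assumed rates, harm is missed in 55-76% of trials at 10% v 30%, 79-93% at 5% v 15% and 65-81% at 20% v 40%, but in only 13-35% at 20% v 60%. These figures assume 20 to 25 per arm, a two-sided 5% level and Fisher or uncorrected chi-squared. A reader might also conclude that the adverse-event test is the only comparative safety analysis. It is not, but the mean-difference and estimating-equation analyses are significance tests too and add no safety criterion. This should be corrected before the data are analysed; it does not call the design or the efficacy analysis into question.

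**What to change.** In the Safety assessment of Section 2.9:

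- Make the main adverse-event comparison the proportion of patients with events in each arm with exact 95% intervals, and the between-arm risk difference with a 95% interval (for example Newcombe), interpreted by its upper limit.
- Give mean differences with 95% intervals for continuous safety items.
- State that a non-significant test is not evidence of safety. The tests may stay as supporting information.

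In Sections 1.1 and 2.3, restate the safety aim as describing and estimating the safety of adding acupotomy to NBT.

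The cost is wording in three places and a few interval calculations on data already to be collected, with no more patients. The downside is that the trial can no longer claim to have verified safety.
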